### Sample size calculation

The power analysis was performed for a 2 (between-subjects, treatment vs. control) × 5 (within-subject, measurements T0–T4) design where the primary focus was the interaction effect between the treatment and the time variable. We used G*Power [38]. In order to be able to find an effect of *η*
_*p*_
^2^ = 0.03 with a test power of 1 − *β* = 0.80, which falls between what is considered a small and medium effect size [39], a total sample of 44 participants is needed.

Based on Cooper and Conklin, we assume a non-negligible dropout rate [40]. Therefore, we planned to assign 30 participants to both the treatment and control conditions, summing to a total sample of *n* = 60.

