### Statistical methods

The aim of the study is to analyze the efficacy of the intervention in terms of improvement of self-efficacy as well as mental and physical health. This will take place in comparison between the intervention and control group. In the evaluation, we will perform an analysis of covariance (ANCOVA) with the outcome measured at T1 and the baseline scores of T0.

First of all, the analyses will be performed according to the intention-to-treat principle. Missing data will be imputed. Therefore, SPSS multiple imputation, module employing “monotone missing pattern” and incorporating complete data for sex, age, and baseline measurements of primary and secondary outcomes are used. We do not plan interim analyses.

Secondly, to evaluate the sustainability of the effects in comparison of both groups (between-subject factor) and of the different measurement points (T0–T4; with-subject factor) mixed ANOVAs will be conducted. In case of massive violations of normality, we will resort to robust methods such as generalized estimating equations. In case of violation of assumption of sphericity, we will use Huynh–Feldt or Greenhouse–Geisser corrections. Further descriptive analyses will assess treatment motivation, expectations, satisfaction, clinical data, and sociodemographic data. To illustrate potential group differences, *t*-tests and χ^2^ tests will be used. In case of non-normality or small cell sizes, the Mann–Whitney *U* tests or Fisher’s exact tests will be used. Further potential exploratory analyses might include subgroup comparisons, such as sex differences, dropouts, or participants who have the most benefit. Third, we would like to explore possible correlations and association patterns using regression analysis or network analysis. The documentation of adverse events and serious adverse events is conducted in separate tables and line listings for comprehensive analysis to ensure the highest level of safety, although we do not anticipate any serious or adverse events. However, should any unexpected serious adverse events occur (such as suicidal risks or severe depressive symptoms), participants will have access to expert consultation from the study team to ensure they receive the necessary support.

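### The group-by-time interaction over T0–T4 cannot by itself show lasting benefit, and GEE without a small-sample correction would be a poorly calibrated fallback

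*Protocol article*

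**What the plan says.** The Statistical methods section separates two analyses. The first is an ANCOVA of the T1 score adjusted for T0, which matches the primary outcome. The second is meant "to evaluate the sustainability of the effects in comparison of both groups (between-subject factor") and over time, with T0–T4 as the within-subject factor. The method and its fallback for non-normality are given together: "mixed ANOVAs will be conducted. In case of massive violations of normality, we will resort to robust methods such as generalized estimating equations".

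The Sample size calculation section describes the same 2×5 layout as one "where the primary focus was the interaction effect between the treatment and the time variable". No section states which comparison at 3, 6 or 12 months would count as sustained benefit.

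A second contingency concerns the covariance structure: "In case of violation of assumption of sphericity, we will use Huynh–Feldt or Greenhouse–Geisser corrections". The working correlation, variance estimator and reference distribution for GEE are not given.

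**The concern.** There are two separate problems.

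**The question and the test do not match.** The interaction has 4 degrees of freedom and asks whether the arm difference changes anywhere between T0 and T4. Because T0 precedes treatment, an effect at T1 alone is such a change. A benefit that is gone by T2 and a benefit that holds for a year can both give a small p-value. If that p-value were read as evidence of sustained effect, a short-lived gain could be reported as lasting. The mixed ANOVA is the only analysis that the article assigns to comparing the arms over follow-up.

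**The fallback does not address its trigger.** GEE models means, so skewness and outliers act on its estimates as they do on those of the ANOVA. What it adds is a sandwich variance that does not rely on the assumed covariance, and that variance is justified by a large number of independent patients. Here there are 60 at most, and 44 if dropout uses up the whole margin.

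**Working it through.** **Inputs.** From the article: 2 arms, 5 visits, 30 per arm planned, 44 in total (22 per arm) required, partial eta squared 0.03, power 0.80. Assumed because not stated: two-sided alpha 0.05, correlation rho = 0.5 with equal variances and covariances, complete data, SD = 1. The 0.8 SD effect is illustrative.

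**1. The plan's own figure.** f² = 0.03/0.97 = 0.0309. The noncentrality is λ = f²·N·5/(1 − rho) = 0.0309 × 44 × 5/0.5 = 13.61. With the multivariate F (4 and N − 5 = 39 df), power is 0.805 at N = 44 and 0.793 at N = 43, so 44 is reproduced. The univariate version with sphericity needs 40. The stated 44 is not in dispute, and its reproduction supports reading the 4-df interaction as the test the design was built on.

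**2. What the interaction responds to.** Let d_j be the true arm difference at visit j. Under equal correlations,

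λ = (n/2) · Σ(d_j − mean d)² / (1 − rho), with n per arm.

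- T1 only (0, 0.8, 0, 0, 0): the sum is 0.64 × 4/5 = 0.512.
- Sustained (0, 0.8, 0.8, 0.8, 0.8): the sum is 4 × 0.64 × 1/5 = 0.512.
- T4 only (0, 0, 0, 0, 0.8): the sum is again 0.512.
- Fading (0, 0.8, 0.4, 0.2, 0): the sum is 0.84 − 5 × 0.28² = 0.448.

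The first three are identical. At n = 30, λ = 15 × 0.512/0.5 = 15.36; for the fading pattern it is 13.44.

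The 1-df comparison is the arm difference in change from T0 to T4. Its standard error at n = 30 is √[(2/30) × 2 × (1 − 0.5)] = 0.258, so a difference of 0.8 at T4 is 3.10 standard errors.

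| Pattern, 30 per arm | Interaction, univariate F | Interaction, multivariate F | T0-to-T4 contrast (t test) |
|---|---|---|---|
| T1 only | 89.2% | 86.9% | 5.0% |
| Fading to zero | 84.2% | 81.5% | 5.0% |
| Sustained T1–T4 | 89.2% | 86.9% | 86.1% |

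At 22 per arm, the univariate interaction gives 76.0% for both the T1-only and the sustained pattern. The contrast gives 5.0% and 73.6%. Simulation with 4,000 runs per pattern agrees: at 30 per arm the interaction rejects 88.9% for T1 only, 84.5% for fading and 89.5% for sustained.

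**3. Type I error of uncorrected GEE.** With complete data, equal arms and a separate mean for each arm and visit, GEE reproduces the arm-by-visit means. Its sandwich variance is then the sample covariance with divisor n instead of n − 1. The Wald statistic is therefore T²·n/(n − 1), where T² is Hotelling's statistic. With normal errors the rejection rate at nominal 5% is exact:

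P{F(4, 2n − 5) > 9.488 · [(n − 1)/n] · (2n − 5)/[4(2n − 2)]}.

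- n = 30: threshold 9.488 × (29/30) × 55/232 = 2.174, rate **8.4%**.
- n = 22: threshold 9.488 × (21/22) × 39/168 = 2.102, rate **9.9%**.
- Single contrast: the threshold is 1.960·√[(n − 1)/n] on t with 2n − 2 df. This gives 5.9% at n = 30 and 6.2% at n = 22.

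Simulation (10,000 runs per setting, normal and exponential errors, equal or autoregressive correlations) gives about 8–9% at 30 per arm and 9.2–10.1% at 22.

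**4. The methods it would replace or could use.** At 22–30 per arm, with exponential errors, the mixed ANOVA rejects 4.6–5.2% under equal correlations. With the Greenhouse–Geisser correction it rejects 3.9–4.9% across both correlation structures. Without that correction it rejects 7.0–7.5% under autoregressive correlation, so the plan's sphericity provision matters. The Hotelling F-test gives 4.2–5.1% throughout.

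In a smaller check with fitted GEE models (600 runs, standard error about 1 point), the uncorrected sandwich gave 10.3% at 30 per arm and 10.0% at 22. Model-based variance under the correct working correlation gave 5.5% and 6.0%. A bias-reduced sandwich still referred to chi-square gave 9.0% and 8.2%, so the reference distribution matters as well as the variance.

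**The case against.** The article does not say that one omnibus p-value will decide sustainability. It speaks of mixed ANOVAs in the plural, the interaction focus comes from the power section, and follow-up contrasts may be in a statistical analysis plan that is not shown. This stands. A reader might infer that nothing but the interaction will be examined, but the text does not go that far. What remains is that the method named for the purpose does not answer the question by itself.

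Including T0 is not an error. Without it, a constant benefit over T1–T4 would produce no interaction at all. The test is sensitive to lasting benefit; it is just not specific to it.

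A reader might also infer that the plan inflates type I error. The documents do not support that as a flat statement. GEE is given only as an example, only after marked non-normality, and with no variance estimator fixed. The inflation belongs to the uncorrected sandwich with a chi-square reference, and it is mostly a feature of the 4-df test: for the single contrasts recommended here it is about one percentage point. The 22-per-arm figures apply only if the analysed sample shrinks to 44, whereas the article plans intention-to-treat analysis with imputation.

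Nor does the point reach every secondary outcome. By Table 1, eight of the twelve are scheduled in both arms from T0 through T2–T4. Sense of coherence is measured at baseline only, and satisfaction, motivation and expectation are collected in the intervention arm only.

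**Conclusion.** The point holds in a limited form. The interaction over T0–T4 is as likely to be significant for an effect confined to T1 as for one lasting to T4: roughly 87–90% each for 0.8 SD at 30 per arm. By itself it cannot support a claim of sustained benefit. The exact equality rests on equal correlations; other structures would change the percentages, but not the fact that the test also responds to a T1-only effect.

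The fallback is badly matched to its trigger. If it were run with an uncorrected sandwich and a 4-df chi-square test, it would reject about 8–9% at 30 per arm and 9–10% at 22, where the F-based tests stay near 5% even with skewed errors. These figures assume complete data and do not model the planned imputation.

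The point concerns the GSES and the eight secondary scales followed in both arms. The trial calls itself exploratory, this is a secondary analysis, and the primary ANCOVA at T1 is untouched. The change is worth making because it is cheap and guards against reporting a short-term effect as a lasting one.

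**What to change.** - Make the baseline-adjusted arm differences at T2, T3 and T4, each with a 95% CI, the sustainability analysis.
- Estimate them from a repeated-measures mixed model of T1–T4 with arm, visit, arm-by-visit, baseline score and baseline-by-visit, an unstructured covariance, REML, and Kenward–Roger or equivalent degrees of freedom.
- For non-normality, keep this model and add a bootstrap or permutation check.
- If GEE is used, require a small-sample-corrected variance together with a t or F reference.
- State that this covers the GSES and the secondary scales measured in both arms at T0–T4.

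The cost is analysis-plan wording and slightly more modelling work. No new data, patients or visits are needed. With this sample size the unstructured covariance may fail to converge, so a simpler structure should be named in advance.

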### Ethical aspects

The study is conducted in accordance to the guidelines of the Declaration of Helsinki and approved by the local Ethics Committees of the University Hospital Essen (22–10,844-BO). In the event of important protocol modifications, the study center will immediately inform the ethics committee and, if necessary, the sponsor and participants. In addition, we will update the protocol in the clinical trial registry.

### Roles and responsibilities

The clinical trial oversight involves several key groups. The coordinating center, steering committee, and data management team take place through the Clinic for Psychosomatic Medicine and Psychotherapy, LVR-University Hospital. The coordinating center manages overall operations, communication, and quality control, while the steering committee provides strategic guidance and ensures scientific and ethical oversight. The data management team focus on unbiased endpoint evaluation and data quality, ensuring the trial meets regulatory and scientific standards. Additional teams are the Ethics Committees of the University Hospital Essen, which ensure the trial approval and ongoing ethical compliance.

## Discussion

The POSITIV trial is, to our knowledge, the first randomized controlled trials for patients with post COVID- 19 and psychological burden using respiratory biofeedback training and cognitive behavioral group therapy as intervention.

What is unique about the presented intervention is that it is based on the consideration of the multifactorial pathogenesis of post COVID- 19 [41–46]. For this reason, patients in the intervention group will receive respiratory biofeedback training, which can influence by learning processes the autonomic nervous system, in addition to cognitive behavioral group therapy to support coping with the disease. Thus, the aim is to improve patients’ self-efficacy in comparison to the control group.

Since COVID- 19 spreads worldwide, the number of people with sequelae symptoms after infection increases. As somatic symptoms, impairments of the autonomic nervous system (ANS) appear to be common in post COVID- 19 patients [47, 48]. An ANS dysfunction can course changes in the regulating of physiological functions as respiration, blood pressure, heart rate, or digestion [48].

The main central nervous regulator of the ANS is the hypothalamus with its nuclei as well as the brainstem with the regions of midbrain, pons, and medulla oblongata [49, 50]. The exact pathomechanisms of ANS dysfunction after COVID- 19 are still speculative. Different studies in the last year focused on potential mechanism behind autonomic dysfunction of post COVID- 19, identifying neuroinflammation, autoimmunity, and disruption in the renin-angiotensin system or endothelial damages as key contributors [48, 51, 52]. Dani et al. hypothesize that the autonomic nervous system may be disrupted by viral or immune-mediated mechanisms, leading to either transient or persistent orthostatic intolerance syndromes [51]. In the therapy of ANS dysregulation, biofeedback methods are used for self-regulation. Studies show a significant improvement in biofeedback training for stress-related disorders such as post-traumatic stress disorder, depression, or panic disorders [53, 54]. In addition, an efficacy in combination with cognitive behavioral therapy could be shown. Changes were visible after 4 weeks of training [53]. Due to the altered respiratory regulation caused by the impairment of the ANS, and based on the previous research results, we integrated the respiratory mobile biofeedback treatment as a part of the study intervention.

Many post COVID- 19 symptoms cause difficulties in individuals’ functioning levels. Furthermore, this often leads to additional psychological burden due to worries, anxiety, and fears about the course of the disease [55, 56].

The German guidelines for treatment of post and long COVID- 19 recommended to consider diseases and dysfunctional coping strategies in the treatment of post COVID- 19 psychological symptoms [17, 57]. Prior studies on rehabilitation treatment of post COVID- 19 patients showed significant benefits of including individual and group psychotherapy (CBT), individualized aerobic exercise training, body awareness training, breathing therapy, relaxation techniques, cognitive training, and social counseling as core elements [45, 58]. A Dutch RCT study investigating the effect of CBT on post COVID patients with fatigue demonstrated that participants reported improvements in physical resilience and social life [59, 60]. The positive effects of the therapy persisted for up to 1 year after the intervention, highlighting the sustainability of CBT in treating long COVID symptoms [61].

Studies also showed that post COVID- 19 patients have a clinically significant psychological burden, and that such treatment concept could help to reduce this kind of distress [45, 58], which is why we decided to develop and assess further psychological treatment possibilities.

In the execution of this RCT, there are challenges to consider. First, post COVID- 19 patients exhibit a very heterogeneous symptomatology both somatically and psychologically. Yet, a concentration deficit as well as a fatigue complex appears to be very central and quite common [62]. This can result in difficulties in a proper utilization of treatment options due to, e.g., restrained ability to travel. Second, a requirement is the technical equipment for participation in the group therapies, which constitutes a further limiting factor.

In conclusion, this trial might improve our knowledge about a treatment of bodily distress disorder in COVID- 19 recovered persons. This knowledge could be helpful in the health care of patients with the post COVID- 19 condition.

## Trial status

The trial is registered in the German Clinical Trial Register (DRKS; DRKS-ID: DRKS00030565). This study protocol is the first version for this specific trial. The recruitment started on October 5 th of 2022. Approximately the recruitment is completed in September 2023. Recruitment is complete when the paper is submitted. This was due to the clinic’s urgent care for post COVID- 19 patients. It was necessary to provide prompt and rapid care to the burdened patients, who could not wait for a publication to be completed. End of September 2024, the complete follow-up will be finished.

## Data Availability

Study data will be published and made available to the scientific community after the assessments are completed.

## Abbreviations

ANS: Autonomic nervous system
CBT: Cognitive behavioral therapy
C-TNBS: Center for Translational Neuro- and Behavioral Sciences
CSQ: Client Satisfaction Questionnaire
DRKS: “Deutsches Register Klinischer Studien” (German Clinical Trials Register)
DSM- 5: Diagnostic and Statistical Manual of Mental Disorders
e.g.: Exempli gratia, for example
EU-DSGVO: “EU-Datenschutz-Grundverordnung” (EU General Data Protection Regulation)
GAD- 7: Generalized Anxiety Disorder Scale-7
GSES: General Self-Efficacy Expectancy Scale
IES-R: Impact of Event Scale—Revised
PCS-Scale: Post COVID Syndrome—Scale
PHQ- 8: Patient Health Questionnaire Depression Scale
RCT study: Randomized controlled trial study
SOC-L9: Sense of Coherence Scale—Leipzig Short Form
SSD- 12: The Somatic Symptom Disorder—B Criteria Scale
SSS- 8: Somatic Symptom Scale-8
TAU: Treatment as usual
WHO: World Health Organization
WHOQOL-BREF: World Health Organization Quality of Life-BREF
